## Abstract

**Introduction:**

This study aims to investigate patterns of antibiotic treatment-seeking, describe current levels of and drivers for antibiotic use for common infections (respiratory tract and urinary tract infections) and test the feasibility of determining the prevalence and epidemiology of antimicrobial resistance (AMR) in rural areas of Anhui province, in order to identify potential interventions to promote antibiotic stewardship and reduce the burden of AMR in China.

**Methods and analysis:**

We will conduct direct observations, structured and semistructured interviews in retail pharmacies, village clinics and township health centres to investigate treatment-seeking and antibiotic use. Clinical isolates from 1550 sputum, throat swab and urine samples taken from consenting patients at village and township health centres will be analysed to identify bacterial pathogens and ascertain antibiotic susceptibilities. Healthcare records will be surveyed for a subsample of those recruited to the study to assess their completeness and accuracy.

**Ethics and dissemination:**

The full research protocol has been reviewed and approved by the Biomedical Ethics Committee of Anhui Medical University (reference number: 20170271). Participation of patients and doctors is voluntary and written informed consent is sought from all participants. Findings from the study will be disseminated through academic routes including peer-reviewed publications and conference presentations, via tailored research summaries for health professionals, health service managers and policymakers and through an end of project impact workshop with local and regional stakeholders to identify key messages and priorities for action.

Strengths and limitations of this studyThis innovative cross-disciplinary study will combine qualitative, microbiological and epidemiological methodologies to investigate drivers of antimicrobial resistance (AMR) in rural China.It will systematically document key drivers of, and patient pathways leading to, antibiotic use and establish the feasibility of microbiological testing and epidemiological monitoring for AMR and antibiotic use at frontline medical settings in rural China.The mixed methods approach will provide a comprehensive picture of factors influencing prescribing and sampling practices so that bias arising from any individual dataset can be accounted for in the analysis and interpretation of results strengthened through triangulation.The study area, though selected to be representative of rural populations in China, only includes three rural counties of 105 counties in Anhui province. As such, results may have limited generalisability.Nonetheless, the study will identify modifiable influences on current treatment-seeking pathways leading to antibiotic use and determine the feasibility of measuring and monitoring AMR in rural populations; these findings will inform efforts to reduce inappropriate prescribing and improve antimicrobial stewardship.

## Introduction

The problem of drug-resistant infections is widely acknowledged to be of global public health concern, with non-essential use of antibiotics in humans a major contributor.^1^ There is substantial evidence that antibiotics are overused in the Chinese healthcare system.^2–8^ A range of possible reasons for unnecessary use of antibiotics have been identified, including ‘demand side’ issues such as cultural expectations and social norms leading patients to expect antibiotic treatment and ‘supply side’ issues such as perverse financial incentives for prescribing antibiotics, systemic pressures on healthcare providers and professional norms which lead to overprescribing as a risk-reduction strategy. Of these, service providers may play a dominant role.

Health professionals in the UK and China often claim that antibiotic overuse is driven by patient demand and link this, in turn, to lack of public understanding of antibiotic effectiveness and low public awareness.^9^ Studies in both the UK and China suggest, however, that ‘patient demand’ may actually be a misperception on the part of healthcare providers or a rationalisation of their own antibiotic prescribing practices.^10–13^ A study of self-medication in Hefei City, Anhui province, found an association between higher maternal education, medical insurance cover and non-prescribed use of antibiotics for children’s illnesses.^14^ A UK study of prescribing in primary care showed doctors’ perceptions of patient pressure to be a consistently stronger predictor of prescribing than patients’ actual preferences.^15^ On the other hand, it is not uncommon for doctors in both the UK and China to prescribe antibiotics ‘just in case’, due to a desire to reduce medical, legal and reputational risk in the face of clinical uncertainty.^16 17^

A cluster-randomised survey was conducted during the development of this protocol and 2600 rural residents in 12 counties of Anhui province were asked about self-reported health service-seeking and antibiotic consumption.^18^ Almost three quarters (72.7%) of respondents reported that they would do as told if their doctors let them leave an appointment without prescribing any medicine and only 14.3% had ever asked their doctors to prescribe specific drugs.^19^ Results also suggested that knowledge about antibiotics (which pathogens they can be used to treat and what the potential risks are of using them) was associated with increased purchasing of over-the-counter pharmaceuticals and with reuse of leftover pharmaceuticals from family or friends.

There is evidence from China that health systems, especially remuneration mechanisms, may be important drivers of unnecessary antibiotic use.^20^ Patients are used to paying only for medicines they are given and medicine forms an important source of revenue for all care providers. Historically, remuneration mechanisms have provided a perverse financial incentive for healthcare practitioners to overprescribe antibiotics, particularly at lower levels of the health system.^21^ Recent government healthcare reforms, together with policies such as the Special Antimicrobial Use Rectification programme, have been associated with reductions in antibiotic prescribing at county and higher level public hospitals.^3^ However, current policies aim to reduce overall use (eg, by capping the overall proportion of antibiotic prescriptions at hospitals), but do not necessarily ensure equitable access to essential treatment; restricting overall availability of antibiotics may exacerbate health inequities through its negative effects on access to effective treatment among the poor.^22^

Current policies and interventions mainly focus on antibiotic prescribing, but in many settings, non-prescribed antibiotics are widely consumed. In China, antibiotics are freely available over-the-counter without prescription, but little is known for either urban or rural settings about what prompts people to seek treatment at different health facilities or the role of the informal sector (including self-medication, retail pharmacies, traditional Chinese medicine practitioners, unqualified biomedicine practitioners and home care) in the management of infections.

Microbiological facilities are not available at most frontline healthcare settings. Most research on antimicrobial resistance (AMR) in China has, therefore, drawn on patient data collected in urban teaching hospitals. Because patients can choose to attend facilities at any level of the three-tier health system (community clinics, township health centres or county-level hospitals) and care pathways do not follow a predictable pattern of upwards referral, the extent to which antibiotic prescribing in urban hospitals drives the spread of antibiotic resistance in the wider population is currently unknown. The often asserted high burden of AMR in China may be misleading since current assumptions are based on potential pathogens isolated in selected microbiology laboratories enrolled in the national surveillance system and it is uncertain if this reflects the incidence of resistance in non-hospitalised patients with mild to moderate infection receiving antibiotics, most of whom do not have samples sent to the laboratory.^23 24^ UK data indicates that 1:35 patients presenting to their General Practitioners (GPs) with acute cough have microbiological sampling and perhaps 1:5 with urinary tract infection (UTI).^25^ This data indicates that resistance rates to key antibiotics based on biased laboratory data may be over-emphasised.^26 27^

There is a need for comprehensive and systematic assessment of prescribing and purchasing practices in the context of China’s unique health systems and policies, to identify potential targets for interventions to optimise prescribing and consumption. There are also crucial gaps in evidence regarding antibiotic resistance and its determinants in rural communities and health facilities at village and township levels in China and it is important to investigate the possibility of introducing routine monitoring of prevalence and epidemiology of AMR in these settings.

### Study aims and objectives

This study aims to investigate levels of antibiotic prescribing and the burden of AMR in rural areas in China and identify key drivers of antibiotic use for common infections in the community, in order to identify potential interventions to promote antibiotic stewardship and reduce the burden of AMR.

The study objectives are summarised in (Box 1).

Box 1Study objectivesAssess feasibility of obtaining community-based samples, isolating common pathogens and determining their antibiotic susceptibilities for presentations of Urinary Tract Infections (UTIs) and Respiratory Tract Infections (RTIs)Estimate prevalence of AMR in non-hospitalised patients and test the hypothesis that community prevalence of AMR is lower than that based on analyses of samples from large urban hospitals with a higher proportion of inpatientsDescribe patient clinical record systems and assess the reliability of information from electronic patient records for monitoring antimicrobial usage and AMRAnalyse microbiological findings in relation to patient-reported symptoms, clinical diagnoses and antibiotics prescribed in clinical facilities;Investigate what types and sources of health care rural residents of Anhui Province seek for common respiratory tract infections from all forms andsources of health care (including informal, Traditional Chinese Medicine)Understand what drives antibiotic provision (both prescribed and purchased without prescription) and consumption for selected conditions at lower levelsof the formal (government-run facilities) and informal (retail pharmacies and any other treatment sources) health care system; andAssess what types ofand targets for intervention are likely to be most effective for optimizing antibiotic use.

## Methods and analysis

### Study design

This is a mixed-method study comprising two main components: a microbiological feasibility study and clinical record review (objectives 1–4) and a qualitative study of antimicrobial prescribing and purchasing practices (objectives 5–7).

### Setting

This study is being implemented in three rural residential areas in Anhui province, including one village clinic, one township health centre and all local retail pharmacies (4–8) within each area. One of the three areas will be used to pilot the study. Anhui province is located in northeast China and has a population of 68.6 million of whom 57% live in rural areas. Per capita GDP and income in Anhui rank in the middle (14th) among all provinces in the nation. Its social, cultural and economic background is representative of over 80% of the population in China. There are 968 hospitals, 1941 community and 1398 township health centres and 15 288 village clinics in the province (Annual Health Anhui Statistics 2014). As in most other provinces, there is no strict referral system in Anhui and patients may choose from any level and kind of caregiver, though medical insurance systems enact a 10%–20% decreasing reimbursement ratio for direct medical expenditures incurred at primary care settings upward. In terms of first time medical care, 62.9% is at village or community clinics, 17.3% at township or community health centres and 13.6% at county level hospitals (Annual Anhui Health Statistics 2014).

### Participants

The microbiological substudy aims to recruit a total of 1550 patients (1000 with exacerbation of chronic obstructive pulmonary disease (COPD) and 555 with UTI). We estimate that this will yield 200 *Escherichia coli* isolates and 100 *Streptococcus pneumoniae* isolates, which should provide sufficient power to allow us to estimate key antibiotic susceptibilities (objective 4), on the assumption that:

40% of UTI samples will yield a pathogen.25% of COPD samples will yield a pathogen.90% of pathogens isolated from urine will be *E. coli.*40% of pathogens isolated from sputum will be *S. pneumoniae.*In *E. coli*, resistance to nitrofurantoin, fosfomycin and co-amoxiclav will be <5% and resistance to cephalosporins and fluoroquinolones 50%–60%.^28^In *S. pneumoniae*, penicillin resistance will be 12.5% and erythromycin resistance 90%.^29^

Inclusion criteria of patients are male or female who are: (1) 18 years or older and able to give consent to participate in the microbiological study, exit survey and/or follow-up interviews; (2) presenting to the recruitment site for his/her current illness for the first time during the study period and (3) diagnosed by the attending doctor as having one or more of the following: UTI, exacerbation of COPD, upper respiratory tract infection (RTI) with productive cough and sore throat. These patients will be selected via ‘consecutive sampling’ in which, when a start date has been determined, the recruitment continues daily (7 days a week) thereafter, between 08:00 and 17:00 hours or 09:00 and 18:00 hours on alternate days, until the target numbers have been reached. All incoming patients to the site village clinics and township health centres who meet the inclusion criteria during any study day are invited to participate. This is a pragmatic approach to sampling since patient record systems do not allow the flexibility to carry out random sampling, and ongoing recruitment will ensure the most efficient use of staff and resources in this setting.

Qualitative study participants will include: (1) patients visiting the selected village clinics and township health centres during the study period; (2) customers visiting the selected retail pharmacies during the study period; (3) doctors within the clinics or health centres for treatment of RTIs/UTIs; (4) salespersons working within the selected retail pharmacies.

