### Data collection

#### Specimen collection and microbiological testing (objectives 1, 2 and 4)

The study will collect sputum, throat swab and urine specimens for pathogen identification and susceptibility testing. Sputum will be collected from RTI patients with productive cough (eg, exacerbation of COPD; throat swabs from patients with sore throat and urine from patients with UTIs. Specimen collection will be performed by the attending doctor and placed into a sterilised tube according to a standard operation protocol. The specimen tubes will be put immediately into a refrigerator and preserved at below –4℃ temporarily prior to being shipped to the Central Laboratory of Anhui Medical University (AMU). At about 12:00 and 17:30 hours each day, the samples in the refrigerator will be transferred to a portable code case filled with ice bags which is then sealed and handed over to a contracted bus company. The company is held responsible for shipping the specimens within a set time limit (within 4 hours).

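### The recruitment target does not add up (1000 + 555 = 1555, not 1550), and its split leaves no place for the upper-RTI and throat-swab patients the study also enrols

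*Protocol article*

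**What the plan says.** In the protocol article, the Participants section gives the target: the substudy "aims to recruit a total of 1550 patients (1000 with exacerbation of chronic obstructive pulmonary disease (COPD) and 555 with UTI". It expects this to yield "200 *Escherichia coli* isolates and 100 *Streptococcus pneumoniae* isolates", and rests on those counts its claim that key susceptibilities can be estimated.

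The yield assumptions cover two patient groups only: "40% of UTI samples will yield a pathogen" and "25% of COPD samples will yield a pathogen". *E. coli* is then taken as 90% of urine pathogens and *S. pneumoniae* as 40% of sputum pathogens.

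Three other statements bring in a further group:

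- The inclusion criteria, in the same section, list a third eligible diagnosis beside UTI and COPD exacerbation: "upper respiratory tract infection (RTI) with productive cough and sore throat". All eligible attenders are invited consecutively, and recruitment runs until the targets are met.
- The section on specimen collection and microbiological testing takes sputum from RTI patients with productive cough, naming COPD exacerbation only as an example, and "throat swabs from patients with sore throat and urine from patients with UTIs".
- The abstract (Methods and analysis) describes the total as "Clinical isolates from 1550 sputum, throat swab and urine samples taken from consenting patients".

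**The concern.** There are two faults of different weight.

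The first is a plain sum: the components do not equal the total.

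The second is that COPD and UTI together already exceed the total by 5, so no places are left for upper-RTI patients or throat swabs. Yet the article enrols the former, collects the latter, and in the abstract counts swabs within the same 1550. The abstract also counts samples where the Participants section counts patients.

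Two things depend on the answer. One is when recruitment stops: upper-RTI patients either have no target of their own or draw on the respiratory 1000. The other is the expected *S. pneumoniae* count. Its inputs were set for COPD sputum, and the article gives no yield for throat swabs or for sputum from upper-RTI patients.

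**Working it through.** **Inputs, all from the Participants section.** Total 1550; COPD 1000; UTI 555; pathogen-positive 25% (COPD) and 40% (UTI); species share 40% (*S. pneumoniae* in sputum) and 90% (*E. coli* in urine); penicillin resistance in *S. pneumoniae* 12.5%.

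**1. The plan's isolate counts.** Expected isolates = patients x proportion positive x species share.

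- *E. coli*: 555 x 0.40 x 0.90 = 199.8, stated as 200.
- *S. pneumoniae*: 1000 x 0.25 x 0.40 = 100, as stated.

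Both reproduce from the stated split.

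**2. The total.** 1000 + 555 = 1555, which is 5 more than 1550 (5/1550 = 0.3%). Working back from the *E. coli* target, 200/(0.40 x 0.90) = 555.6. That accounts for the 555 and suggests that the total, not the component, is the slip.

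**3. Does the gap of 5 matter for yield?** Suppose 1550 were kept by trimming one group:

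- 550 UTI: 550 x 0.40 x 0.90 = 198 *E. coli*.
- 995 COPD: 995 x 0.25 x 0.40 = 99.5 *S. pneumoniae*.

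It does not.

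**4. Can the abstract and the Participants section both hold?** With one specimen per patient, 1550 samples that include throat swabs cannot also be 1000 sputum plus 555 urine. With two specimens from some patients, 1550 patients are not 1550 samples. On either reading one statement needs rewording.

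**5. What if upper-RTI patients shared the 1000 places?** Let s be their share and y the proportion of them yielding *S. pneumoniae*. The documents give neither, so both are assumptions here. The COPD assumption amounts to 0.25 x 0.40 = 0.10 per patient, so

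expected isolates = 1000(1 - s) x 0.10 + 1000 x s x y.

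In the worst case, y = 0, the 95% half-width for 12.5% resistance is 1.96 x sqrt(0.125 x 0.875 / n):

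| Assumed share s | Expected isolates n | Half-width (points) |
|---|---|---|
| 0 | 100 | 6.5 |
| 25% | 75 | 7.5 |
| 50% | 50 | 9.2 |

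With y = 0.05 instead, the counts at 25% and 50% are 87.5 and 75. With y = 0.10, the COPD figure, the count stays at 100 whatever the share.

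**The case against.** The strongest reply is that the isolate counts are right. Both reproduce, and the sum error is a copy-edit. The 1000 are described as COPD patients, and the article speaks of target numbers in the plural, so the natural reading is one target per diagnosis, with upper-RTI patients taking no COPD places. The study is also a feasibility study, its analytical work under objective 4 depends on sample size, and it states no precision target that a smaller isolate count would breach.

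Most of this stands. A reader might infer that the 100 *S. pneumoniae* isolates do not follow from the stated sample. They do, exactly. A reader might also infer that the count will fall short. The documents do not show that: they never say that places are shared, the shares and recovery rates above are assumptions, and upper-RTI patients with productive cough would give sputum, for which no yield is stated. Nor do the documents say that isolates from two specimens of one patient would be counted twice; removal of duplicates is commonly left to the analysis plan.

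What the reply does not remove is the conflict in the text. Separate targets are a reasonable reading of the Participants section, but that section gives no number for a group it enrols, and the abstract places throat swabs inside the same total. This is not detail left to a fuller document: the article itself states the total, the split, the eligibility and the stopping rule, and they do not agree.

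**Conclusion.** The point holds in two parts. The total is wrong as written, by 5 patients or 0.3%, with no material effect on either isolate count. The substantive part is that the target has no place for upper-RTI and throat-swab patients, whom the article enrols and whose swabs the abstract counts within the 1550.

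The expected 100 *S. pneumoniae* isolates are correct on condition that all 1000 respiratory places go to COPD patients giving sputum, which the wording does not secure. Any loss is conditional on places being shared and on a lower yield in the patients who share them. Its size cannot be derived from the documents; the worked figures only show its scale under stated assumptions.

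**What to change.** - **Participants section, total.** Correct it to 1555 patients.
- **Participants section, who counts.** State that 1000 (COPD exacerbation, sputum) and 555 (UTI, urine) are separate stopping targets. Say that upper-RTI and throat-swab patients recruited over the same period are counted outside both, with no yield claim. If they are meant to count inside the 1000, say so and restate the expected *S. pneumoniae* count by specimen type, with the assumed yields.
- **Abstract.** Distinguish patients from samples and take throat swabs out of the COPD-plus-UTI total. Changing 1550 to 1555 alone would create a new contradiction, because that sentence lists throat swabs.

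The change is to wording and should be settled before recruitment closes, because it decides when recruitment stops. The cost is either a possibly less favourable stated isolate count, if places are shared, or throat-swab cultures shown openly as additional to the stated total, if they are not.

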### Data collection

#### Specimen collection and microbiological testing (objectives 1, 2 and 4)

The study will collect sputum, throat swab and urine specimens for pathogen identification and susceptibility testing. Sputum will be collected from RTI patients with productive cough (eg, exacerbation of COPD; throat swabs from patients with sore throat and urine from patients with UTIs. Specimen collection will be performed by the attending doctor and placed into a sterilised tube according to a standard operation protocol. The specimen tubes will be put immediately into a refrigerator and preserved at below –4℃ temporarily prior to being shipped to the Central Laboratory of Anhui Medical University (AMU). At about 12:00 and 17:30 hours each day, the samples in the refrigerator will be transferred to a portable code case filled with ice bags which is then sealed and handed over to a contracted bus company. The company is held responsible for shipping the specimens within a set time limit (within 4 hours).

On arrival of any batch of specimens at AMU central lab, a designated technician will perform standard specimen assessment and pretreatment and then bacteria inoculation, identification and susceptibility tests. Sputum and throat swab specimens will be inoculated on four plates (a blood agar plate, a MacConkey agar plate, a chocolate agar plate and a chrome agar plate); and urine specimens inoculated on two plates (a blood agar plate and a MacConkey agar plate). The inoculated blood agar and chocolate agar plates will be cultured and incubated in an atmosphere of 5% CO_2_ at 35°C; the MacConkey agar and the chrome agar plates, incubated in air at 35°C. The incubation time will be 18–24 hours plus an additional 24 hours if no bacteria are observed for the first period. Bacteria identification will use automated methods, that is, the MicroscanWalkaway-96 System with PC33 (for gram-positive bacteria) or NC50 (for gram-negative bacteria) kits and also according to different biochemical reactions as follows: (1) *E. coli* chrome agar/VITEK2 or MALDI-TOF; (2) *S. pneumoniae* optochin/biochemistry; (3) *Haemophilus influenzae* X+V factors or MALDI-TOF and (4) *Moraxella catarrhalis* MALDI-TOF. For the bacteria susceptibilities, automated methods will be used (VITEK2 and MicroScan Walk Away 96 plus) along with disk diffusion and agar dilution methods (according to CLSI). Multidrug resistance will be defined according to standard criteria as set out by Magiorakos *et al*.^30^Antimicrobial susceptibility data on the key pathogens identified in community sampling will be extracted from the existing diagnostic laboratory databases for comparison with isolates from village clinics and county hospitals. A timeline for data collection can be found in online supplementary appendix table 1; a full list of bacterial isolates and susceptibility testing can be found in online supplementary appendix table 2.

10.1136/bmjopen-2018-027819.supp1Supplementary data

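### The specimen storage rule pairs a refrigerator with a sub-zero temperature, and on alternate days recruitment outlasts the last pick-up by half an hour

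*Protocol article*

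**What the plan says.** All of this is in the Protocol article.

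- **Storage** (Specimen collection and microbiological testing): "The specimen tubes will be put immediately into a refrigerator and preserved at below –4℃ temporarily". The rule covers sputum, throat swabs and urine.
- **Pick-up and transport** (same section): "At about 12:00 and 17:30 hours each day, the samples in the refrigerator will be transferred" to a portable case with ice bags, and a bus company must deliver "within a set time limit (within 4 hours".
- **Laboratory** (same section): "On arrival of any batch of specimens at AMU central lab, a designated technician will perform standard specimen assessment and pretreatment", followed by inoculation. The article describes no thawing step.
- **Recruitment hours** (Participants): "between 08:00 and 17:00 hours or 09:00 and 18:00 hours on alternate days".
- **Sample size** (Participants): the plan is to "recruit a total of 1550 patients (1000 with exacerbation of chronic obstructive pulmonary disease (COPD) and 555 with UTI", on the assumptions that "40% of UTI samples will yield a pathogen" and "25% of COPD samples will yield a pathogen". With *E. coli* at 90% of urine pathogens and *S. pneumoniae* at 40% of sputum pathogens, it expects 200 and 100 isolates.
- **Use of the results** (Quantitative analysis): the share of specimens that technicians judge adequately collected, stored and transported is a feasibility measure for objective 1. Pathogen-positive percentages are estimated and compared with urban hospital data under objective 2.

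**The concern.** The storage sentence cannot be followed as printed. A refrigerator chills without freezing, and a temperature below –4 °C is sub-zero. The steps on either side, ice bags and then direct inoculation, fit chilled storage rather than frozen.

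Three things depend on the rule:

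- **Isolate counts.** They are products of culture yield with no allowance for lost viability, so any loss passes straight through to them.
- **Positivity.** An organism that dies in storage is recorded as no pathogen. That lowers community positivity and affects the comparison with hospital data. Resistance percentages are calculated among isolates, so there the main effect is lost precision. They would be biased only if survival differed with resistance.
- **Feasibility.** Adequate preservation needs one coherent standard. As printed, a tube kept at ordinary refrigerator temperature breaks the temperature rule, and a tube that obeys it may be unfit for culture.

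The timing gap is a separate and smaller matter. On the days that run to 18:00, specimens taken after the last pick-up have no described route to the laboratory until about noon the next day.

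**Working it through.** **1. The plan's own isolate counts (inputs from Participants).**
Expected isolates = patients × culture yield × species share.
- *E. coli*: 555 × 0.40 × 0.90 = 199.8, matching the stated 200.
- *S. pneumoniae*: 1000 × 0.25 × 0.40 = 100.0, matching the stated 100.

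**2. Storage text set side by side.**

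| Step | What it implies |
|---|---|
| Refrigerator | chilled, above freezing |
| Below –4 °C | frozen |
| Case with ice bags | chilled |
| Inoculation on arrival, no thaw step | unfrozen, viable specimen |

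The temperature figure is the only one of the four that implies freezing.

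**3. What a loss of yield would do.** The documents give no loss rate, so L below is an assumption shown as a range. Isolates = step 1 × (1 – L). Patients needed to restore 200 and 100 are 200 / [0.36 × (1 – L)] for UTI and 100 / [0.10 × (1 – L)] for COPD, rounded up. The last column is the 95% half-width at the plan's 12.5% penicillin resistance, 1.96 × √(0.125 × 0.875 / n), with n the *S. pneumoniae* isolates.

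| L (assumed) | *E. coli* | *S. pneumoniae* | UTI / COPD patients needed | Half-width |
|---|---|---|---|---|
| 0% | 199.8 | 100 | 556 / 1000 | 6.5 points |
| 10% | 179.8 | 90 | 618 / 1112 | 6.8 points |
| 25% | 149.9 | 75 | 741 / 1334 | 7.5 points |
| 50% | 99.9 | 50 | 1112 / 2000 | 9.2 points |

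This shows how sensitive the plan is to L. It does not predict L.

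**4. Time from collection to arrival at the laboratory.** Time = wait for the next pick-up + up to 4 h of transport.
- Taken at 08:00: 4 + 4 = 8 h.
- Taken just after 12:00: 5.5 + 4 = 9.5 h, the longest for any specimen that catches a same-day pick-up.
- Taken just after 17:30: 18.5 + 4 = 22.5 h.
- Taken at 18:00: 18 + 4 = 22 h.

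**5. Share affected.** Each two-day cycle has 9 + 9 = 18 recruitment hours, of which 0.5 h falls after 17:30. The share is 0.5 / 18 = 2.8%. The stated components sum to 1000 + 555 = 1555, and 1555 × 0.5 / 18 = 43.2, so about 43 patients if arrivals are uniform.

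**6. Worst case for the timing gap.** If every late specimen were lost: 199.8 × (1 – 0.5/18) = 194.3 and 100 × (1 – 0.5/18) = 97.2.

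**The case against.** **The temperature is probably a misprint, and staff using a refrigerator would not freeze anything.** This is a fair reading, since the equipment, the ice bags and the absence of a thaw step all point to chilled storage. A reader might infer that the study does freeze its specimens. The documents do not support that: they contain a contradiction, and actual practice is not shown. The printed figure still needs correcting, because it covers every specimen and a team following the article could act on it.

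**The detail belongs in a standard operating protocol outside the article.** That protocol is cited for collecting the specimen and placing it in a tube. The storage temperature is given in the article's own sentence, and that figure conflicts with the equipment named beside it.

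**Safeguards exist.** Specimens are assessed on arrival, one of the three areas is a pilot, and preservation quality is itself reported. These could reveal visibly frozen tubes and they weaken the concern. They may not detect organisms that have lost viability, and the assessment needs a coherent storage standard to work from.

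**The yield loss is not quantified.** This stands in full. The documents give no loss from freezing or delay, so only a risk and its direction can be argued.

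**The timing gap is immaterial to the sample size.** This largely stands. Pick-up is only approximately 17:30, late tubes stay in the refrigerator overnight, and 22–22.5 h assumes the full 4 h of transport. Even total loss of these specimens barely changes the isolate counts.

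**Conclusion.** The storage sentence contradicts itself and should be corrected. If its temperature were followed literally, every specimen would be frozen before live culture, with a risk to positivity and to the 200 and 100 expected isolates. The size of that risk cannot be derived from the documents, so it would go too far to conclude that the yield assumptions have failed or that the sample size is inadequate.

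The recruitment and pick-up times also fail to match. The gap affects about 2.8% of recruitment time, or about 43 of 1555 patients assuming uniform arrivals and a pick-up at exactly 17:30. Those specimens could take up to 22–22.5 h to arrive, against at most 9.5 h for the rest, assuming the full 4 h of transport and no other pick-up. A reader might infer that this delay endangers the isolate targets. It does not, because losing all of these specimens leaves about 194 and 97.

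Severity overall is moderate to minor. The temperature conflict carries most of the weight.

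**What to change.** 1. Replace the storage text with one non-freezing range consistent with a refrigerator and ice bags, confirmed by the laboratory. If collection has begun, state what was actually done.
2. Use that range as the standard when technicians judge preservation for objective 1.
3. On the 09:00–18:00 days, set the second hand-over after recruitment closes.
4. Log collection and plating times for each specimen, and report culture yield by hold time, so that any effect of delay can be seen.

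The cost is a short text correction, a slightly later courier slot on alternate days and a little more logging. The design and the recruitment target need not change.
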